#### Participant surveys

Baseline visits will be completed during the inpatient stay or within 1 week of discharge, with follow-up visits at weeks 4, 12, and 24 after hospital discharge. Surveys will assess sociodemographic characteristics and health characteristics hypothesized to predict opioid use disorder risk that are not available in the EMR. The baseline and 24-week survey must be completed in person. The 4 and 12-week follow-up surveys were designed to be completed via mail, in-person, or by telephone. If participants complete all 4 visits, they will be compensated a total of $150, to be disbursed in increments at each visit. All study data will be transcribed from hard-copy questionnaires and source documents into a secure, web-based application for storing, managing, and analyzing study data.

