### Primary outcome

The primary outcome is the development of opioid misuse or opioid use disorder during 24 weeks follow up, as measured by the Composite International Diagnostic Interview-Substance Abuse Module (CIDI-SAM) and/or the current opioid misuse measure (COMM).

The CIDI-SAM is a computer-assisted interview (average test–retest reliability *Κ* = 0.84) that identifies opioid use disorder presence and severity, based on symptom clusters, according to the 5th Edition of the Diagnostic and Statistical Manual of Mental Disorders. [10, 12, 13] The COMM is a 17-item paper survey with 5-point Likert scale response options, which will be used to identify the presence and severity opioid misuse behaviors. In order to determine changes in these behaviors over time, COMM will be administered at each follow up. The COMM has acceptable one-week test–retest reliability and internal validity (Intra-class Correlation Coefficient [ICC] = 0.86; 95% CI 0.77–0.92) [14, 15]. A raw score of greater than or equal to 9 will be considered positive for opioid misuse.

The composite outcome will be positive for participants with positive scores at week 24 on either the CIDI-SAM (opioid use disorder) or the COMM (opioid misuse), and will be negative for participations with neither.

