### Statistical analyses

#### Aims 1 and 2: sample size calculations

Based on an expectation of an at-least 8% incidence in the sample over 24 weeks observation of opioid misuse or an opioid use disorder diagnosis, 221 participants would yield 80% power, at a 5% significance level, with a logistic regression to detect an odds ratio of 2.0 for a change of one standard deviation (SD) in score on the COMM. With a 25% drop-out rate expected, the study aims to recruit a total of 295 participants. While the current proposed work will not be adequately powered to attain significant findings regarding predictors of opioid overdose, examination of this outcome will constitute an exploratory aim.

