#### Aims 1 and 2: analysis

The primary outcome event of this study will be a composite outcome indicating the development or lack of opioid misuse or opioid use disorder within 24 weeks of hospital discharge after traumatic injury. To assess the associations between patient factors and hypothesized risk factors with primary event, t-tests, Wilcoxon rank sum tests, and Chi square tests will be applied to measures that differ between those participants who achieve the primary event and those who do not. The test that is used will be based on numeric (normal or non-normal distribution) or a categorical factor. Any baseline or week 4 variable that is univariately associated with the primary event (p < 0.05) and does not reduce the number of events by more than 5% due to missing data will be considered a candidate variable to be included in the development of a best fit prediction model. The prediction model will be constructed based on a forward step-wise logistic regression model building process with threshold for entry into the model of significantly improving the model at a 0.05 significance level. Including baseline and week 4 variables will allow knowledge of which baseline variables are associated with future opioid misuse or opioid use disorder, and which variables can indicate the beginning of addiction in the hopes to develop a method to intervene before the onset of opioid misuse or opioid use disorder. To control for a possible early drug effect, time-on-opioids will be used as a covariate in the model. The diagnostic ability of the model will be assessed by constructing a receiver operating characteristic (ROC) curve and calculating the optimal sensitivity and specificity to predict primary event based on Youden’s J statistic [34]. A secondary survival analysis will examine variables that are associated with time-to-event, such as overdose or incident misuse detected on study measures.

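### The primary outcome is described and powered as misuse or OUD arising over 24 weeks, but it is scored from week-24 status alone

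*Protocol article*

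**What the plan says.** Three statements in the protocol article describe something that accrues over follow-up.

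- Primary outcome, opening sentence: "The primary outcome is the development of opioid misuse or opioid use disorder during 24 weeks follow up".
- Aims 1 and 2: analysis: a composite "indicating the development or lack of opioid misuse or opioid use disorder within 24 weeks of hospital discharge after traumatic injury".
- Aims 1 and 2: sample size calculations: an expected "at-least 8% incidence in the sample over 24 weeks observation".

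Aim 1 likewise speaks of monitoring for OUD across the 24-week follow-up.

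The scoring rule closes the Primary outcome section: "The composite outcome will be positive for participants with positive scores at week 24 on either the CIDI-SAM" (OUD) or the COMM (misuse), "and will be negative for participations with neither".

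On timing, Participant surveys plans a baseline visit "with follow-up visits at weeks 4, 12, and 24 after hospital discharge", and Primary outcome says that the "COMM will be administered at each follow up", with a raw score of 9 or more positive. Table 1 agrees: COMM at weeks 4, 12 and 24, and CIDI-SAM at baseline and week 24 only.

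Earlier misuse is used in a secondary survival analysis of "time-to-event, such as overdose or incident misuse detected on study measures".

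**The concern.** The description and the scoring rule pick out different people. Someone with a COMM of 9 or more at week 4 or 12, who is negative on both COMM and CIDI-SAM at week 24, has developed misuse within 24 weeks by the stated definition. The scoring rule places that person among the non-events. The secondary survival analysis can count the same person as an event.

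Three things depend on which meaning applies.

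- **Power.** The 8% behind the sample size is worded as a 24-week incidence. The scored endpoint yields a week-24 rate, which cannot exceed the cumulative rate from the same measures.
- **Predictor selection.** The univariate tests and the forward stepwise model would look for predictors of being positive at week 24, not of ever becoming positive.
- **Accuracy of the tool.** The ROC curve and Youden's J use the same coding. A tool that flags a person who misused at week 12 and had stopped by week 24 would be charged with a false positive.

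**Working it through.** **1. Who is affected**

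| COMM at week 4 or 12 | COMM or CIDI-SAM at week 24 | Stated definition (developed within 24 weeks) | Scoring rule |
|---|---|---|---|
| Negative | Negative | Non-event | Non-event |
| Negative | Positive | Event | Event |
| Positive | Positive | Event | Event |
| Positive | Negative | Event | **Non-event** |

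Only the last row is in conflict, and it concerns the COMM component. CIDI-SAM is not given at weeks 4 or 12. The article does not state its look-back window, so an OUD that arose earlier may still be picked up at week 24.

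**2. The plan's own figure**

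Inputs from the sample size section: incidence p = 0.08, odds ratio 2.0 per SD, significance level 5% (taken as two-sided), power 80%, drop-out 25%. For logistic regression with one standardised continuous predictor:

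n = (1.960 + 0.842)² / [p(1 − p)(ln 2)²] = 7.849 / (0.0736 × 0.4805) = 221.96

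The article gives 221, which agrees apart from rounding. Then 221 / 0.75 = 294.7, or 295 recruited. Expected events are 221 × 0.08 = 17.7. Power at 221 is Φ(ln 2 × √(221 × 0.0736) − 1.960) = 79.8%.

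**3. If 8% is cumulative and only week-24 status is scored**

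Let f be the share of 24-week cases still positive at week 24. The article does not give f, so the values below are assumptions. The scored rate is 0.08f, and power is Φ(ln 2 × √(221 × 0.08f × (1 − 0.08f)) − 1.960).

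| f | Scored rate | Events in 221 | Power at 221 | Evaluable n for 80% power |
|---|---|---|---|---|
| 100% | 8.0% | 17.7 | 79.8% | 222 |
| 90% | 7.2% | 15.9 | 75.9% | 245 |
| 75% | 6.0% | 13.3 | 68.7% | 290 |
| 50% | 4.0% | 8.8 | 52.4% | 426 |

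If 8% was meant as the week-24 rate, the first row applies and there is no loss. A cumulative rate above 8% also offsets the loss: 16% cumulative with f = 50% gives 0.16 × 0.50 = 8% at week 24.

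**4. A constraint on any repair**

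The analysis section admits both baseline and week-4 variables as candidates for a single model. The sample size section uses the COMM as the predictor, and Table 1 has no baseline COMM. Under the candidate rule, that predictor can only be the week-4 COMM. If a positive week-4 COMM also counted as an outcome event, the predictor would be part of the outcome. The outcome window and the predictor window therefore have to be set together.

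**The case against.** The scoring rule is explicit, so an analyst would know what to code. It also has some logic. The article says the COMM is repeated to follow change over time, and a week-24 outcome keeps week-4 predictors ahead of the event. Active OUD is excluded at baseline, so OUD found at week 24 did develop during follow-up. If week-24 status is the target, nobody is misclassified. Early misuse is not discarded either, since the survival analysis uses it.

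Much of this stands as a defence of a week-24 endpoint. It does not reconcile that endpoint with the aims, the opening definition, the analysis section and the incidence used for the sample size, which all say something else. A secondary analysis does not change the primary coding.

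Some stronger readings are tempting but not supported.

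- **A definite collapse in power.** One can model correlated COMM visits and arrive well below 50%. The article gives neither visit correlations nor persistence, and its 8% is a floor without a stated derivation.
- **A definite bias toward the null.** This follows only if the cumulative outcome is the target.
- **Heavy early misuse, from the 42% cited in the Background.** That figure comes from patients discharged from an emergency room with an opioid prescription. Misuse near that level here would put the cumulative rate far above 8%, and the power loss would shrink or vanish.
- **Loss of early positives who miss week 24.** The sample size allows for 25% drop-out, and the handling of partial follow-up is normally left to the analysis plan.

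**Conclusion.** The point holds as a contradiction in the current text. The primary outcome is described and powered as an occurrence over 24 weeks and scored as a state at week 24. Participants positive on the COMM at week 4 or 12 and negative on both measures at week 24 are events under one statement and non-events under the other. Because the article fixes the rule, this is not detail left to an analysis plan.

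The number of participants affected cannot be worked out from the article. The power loss is conditional on 8% being the cumulative rate and on the assumed persistence: a few percentage points at 90%, about 11 at 75% and about 27 at 50%. It is zero if 8% was a week-24 rate. The change in what the model and the screening tool predict does not depend on those assumptions.

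**What to change.** Choose one meaning and carry it through.

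**If the outcome is cumulative, as described:**

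- For the model of baseline predictors, score the composite positive if COMM is 9 or more at week 4, 12 or 24, or if CIDI-SAM shows OUD at week 24. This matches the 8% incidence, so 221 evaluable and 295 recruited still give about 80% power for a baseline predictor with an odds ratio of 2.0 per SD.
- For any model with week-4 candidate predictors, count only events after week 4 (COMM at week 12 or 24, CIDI-SAM at week 24), among participants not already COMM-positive at week 4. Restate the expected events and power for this model, since the COMM-based calculation belongs to it.
- Report week-24 status as a secondary outcome.

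**If week-24 status is intended:** reword Aim 1, the Primary outcome section, the sample size section and the analysis section accordingly, and restate the 8% and the power as applying to a week-24 rate.

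**Cost.** No new data are needed, because every COMM score is already planned. The cumulative option is more than a change of wording: the single planned model becomes two with different outcome windows, and the week-4 model has fewer events and fewer participants. Transient early positives would count as events, and the week-24 secondary outcome would show how much they matter.

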### Independent variables

A number of independent variables will be collected throughout the 24 weeks follow up. The inclusion of these measures are based on evidence from literature, and the surveys and interviews with Wisconsin trauma center staff and coordinators that were conducted as an earlier part of this study. The follow up time points were determined by the need to regularly evaluate for ongoing opioid use.

The baseline measures will be assessed for the development of a screening tool that could be administered at the point of care for a traumatic injury. Measures administered at follow up time points will be assessed for the development of a screening tool that could be administered by trauma staff at post-discharge follow up appointments or by primary care after a handoff from a trauma service to a clinical service.

Sociodemographic information (including age, sex, race, place of birth, work status, marital status, and household income and inhabitants) are collected at baseline. Additional baseline measures include: depression screen (PHQ-9); anxiety screen (GAD-7); Opioid Risk Tool (ORT); Social Support Questionnaire (ISEL-12); description of mechanism of injury; whether or not the injury was work related; number of procedures and/or complications associated with the injury; medication allergies; and time spent on an intensive care unit.

Ongoing opioid use after hospital discharge is recorded at each visit in order to establish a Morphine Equivalent Daily Dose (MEDD) per time point, as well as to determine the date of last opioid use.

The Pain Medication Questionnaire (PMQ) [16, 17] is a 23-item instrument assessing prescription use behaviors, whose score is associated with physician assessments of opioid medication risk. The instrument has excellent test–retest reliability (coefficient of stability 0.086); and acceptable internal consistency (Cronbach’s alpha = 0.73). This instrument is collected at each visit in an attempt to determine the optimal time for administering an opioid risk screening tool.

The Post-Traumatic Stress Disorder (PTSD) Check List (PCL-5) is a 20-item checklist that measures symptoms on a 5-point Likert scale. The instrument provides an overall score, and domain scores based on symptom clusters. The PCL-5 is used once at baseline, to evaluate for PTSD symptoms that may have existed at the time of the injury, and again at week 12 to evaluate specifically for PTSD symptoms that may have developed and persisted as a result of the event that caused the traumatic injury.

The Pain Catastrophizing Scale (PCS) [18, 19] asks participants to indicate the intensity of each of 13 thoughts or feelings associated with past pain episodes on 5-point scales. The PCS yields a total score and three subscale scores assessing rumination, magnification and helplessness. The PCS has been shown to have adequate to excellent internal consistency (coefficient alphas: total PCS = 0.87, rumination = 0.87, magnification = 0.66, and helplessness = 0.78). The PCS is administered at baseline to assess pain catastrophizing as close to the time of the injury as possible, and again at week 24 to assess for changes that might occur to pain catastrophizing one the participant is no longer in acute pain.

In addition to the CIDI-SAM, which constitutes the primary outcome, the Alcohol Use Disorders Identification Test (AUDIT-C) [20] will be collected at both baseline and week 24. The AUDIT-C consists of 3 items that are validated to assist in identifying hazardous alcohol consumption patterns.

The Adverse Childhood Experience (ACE) Questionnaire consists of 10 yes/no items that describe scenarios, including childhood abuse, neglect, and household dysfunction. These types of adverse childhood experiences have been strongly correlated with substance misuse and use disorder in adulthood. [21] Since all of the participants in this study are adults, this instrument is administered at week 4, rather than baseline, in an effort to reduce survey fatigue at baseline.

The Brief COPE Inventory (COPE), the Opioid Craving Scale (OCS), the Patient-Reported Outcomes Measurement Information System (PROMIS) Global Health Scale, Pain Intensity and Interference (PEG), and the Perceived Need Inventory (PNI) are all administered at each follow up time point in an attempt to capture changes in various areas that may correlate with opioid tapering and discontinuation. The COPE is a 26-item, 4-point Likert scale survey that measures the type and frequency of coping strategies in 13 different domains, including substance use, religion, emotional support, positive reframing, disengaging, humor, self-blame, etc. The OCS consists of three visual analog scales that measure current craving, craving in risky situations, likelihood of giving into craving. The OCS is a composite measure of craving, which exhibits good internal consistency (Spearman’s rho range from 0.85 to 0.92) and predictive validity of future opiate use [22]. The PROMIS is a 10-item measure of general quality of life, which includes a physical health domain (Cronbach’s α  =  0.81), and a mental health domain (Cronbach’s α  =  0.86) [23]. The PEG and PNI both use 11-item Likert scales. The PEG is a 3-item instrument that measures level of pain, and how that pain interacts with enjoyment of life and general activity. The PNI is a 5-item instrument that measures perceived problems with opioid use, including the need for opioid use treatment and the perceived potential effectiveness of that treatment [24–27].

At the conclusion of the follow up period, data will be collected about each participant’s felony and misdemeanor record, and their prescription drug activity. Felony and misdemeanor records will be obtained from public court records from the Wisconsin Circuit Court Access Program (CCAP). A limitation to CCAP data is that it is only available for offenses that occurred within the state of Wisconsin. Prescription drug activity will be collected from the Wisconsin electronic Prescription Drug Monitoring Database (PDMP). Data on prescription opioid fills can be obtained from Wisconsin and 14 other states (Table 1).

**Table 1 Tab1:** Aim 1 measures and follow-up timeline

Measure title	Baseline	Week 4	Week 12	Week 24
Sociodemographic characteristics	X			
Morphine Equivalent Daily Dose (MEDD)	X	X	X	X
Pain Medication Questionnaire (PMQ)	X	X	X	X
Post-Traumatic Stress Disorder Check List (PCL-5)	X		X	
Pain Catastrophizing Scale (PCS)	X			X
Alcohol Use Disorders Identification Test (AUDIT-C)	X			X
Composite International Diagnostic Interview-Substance Abuse Module for Opioid Use Disorder (CIDI-SAM)	X			X
Patient Health Questionnaire (PHQ-9)	X			
Generalized Anxiety Disorder (GAD-7)	X			
Opioid Risk Tool (ORT)	X			
Social Support Questionnaire (ISEL-12)	X			
Adverse Childhood Experiences (ACE)		X		
Brief COPE Inventory (COPE)		X		X
Current Opioid Misuse Measure (COMM)		X	X	X
Opioid Craving Scale (OCS)		X	X	X
Quality of Life Questionnaire (PROMIS)		X	X	X
Perceived Need Inventory (PNI)		X	X	X
Pain Intensity and Interference (PEG)		X	X	X
WI Circuit Court Access Program (CCAP)				X
WI Prescription Drug Monitoring Database (PDMP)				X

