## Discussion

The primary anticipation is that a parsimonious set of injury-related and historical factors will predict opioid misuse and the development of opioid use disorders during the period of observation and that these screening items are feasibly implemented during the course of the management of the injured patient. While it is not expected that these results will achieve adequate power to indicate statistically significant findings related to opioid overdose and mortality, collected patient factors may demonstrate trends toward predictive value for these outcome as well, which might be further developed in future study. The full project will develop 3 products: (1) a screening tool that describes patient opioid-related risk; (2) an implementation strategy for integrating the developed screening instrument into standard clinical care, and (3) preliminary strategies for interventions to prevent opioid misuse, overdose and addiction to be tested in future study, which will be informed by the AUDIT-C workflow analysis and by opioid-related risk factors identified by traumatic injury patient surveys.

While the primary purpose of the current work is the development of an effective opioid misuse screening tool, an important consideration during the course of the work will be imagining the form that an intervention aimed at preventing opioid misuse might take in future research. This intervention could manifest in a variety of forms, including something similar to ‘brief interventions.’ However, an effective intervention also might relate to effective management of pain, and/or appropriate prescribing and monitoring.

An additional question becomes “at what point should results of screening begin to affect care?” Clearly, appropriate and effective pain management is a primary concern during the acute hospital stay. Effective pain management reduces the likelihood of potentially catastrophic complications, such as pneumonia, heart attack, pulmonary embolism, impaired healing, and injury-related post-traumatic stress disorder [36].

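### The ACE, a fixed childhood history, is scheduled only at week 4 with no later collection, so under the 5% event-loss rule one event case without it is enough to exclude it from the prediction model

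*Protocol article*

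**What the plan says.** All references are to the protocol article.

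- **Content.** Under Independent variables, the ACE "consists of 10 yes/no items that describe scenarios, including childhood abuse, neglect, and household dysfunction". The same paragraph describes a strong correlation between such experiences and adult substance misuse and use disorder.
- **Timing.** Because all participants are adults, "this instrument is administered at week 4, rather than baseline, in an effort to reduce survey fatigue at baseline". The Table 1 row beginning "Adverse Childhood Experiences (ACE" has one mark, under Week 4.
- **Contacts.** Participant surveys plans "follow-up visits at weeks 4, 12, and 24 after hospital discharge". It adds: "The 4 and 12-week follow-up surveys were designed to be completed via mail, in-person, or by telephone". The week 24 survey must be done in person.
- **Outcome.** Under Primary outcome: "The composite outcome will be positive for participants with positive scores at week 24 on either the CIDI-SAM" or the COMM.
- **Use as a predictor.** Under Aims 1 and 2: analysis, a baseline or week 4 variable that is univariately associated with the primary event at p < 0.05 and "does not reduce the number of events by more than 5% due to missing data will be considered a candidate variable" for the stepwise model.
- **Expectation.** The Discussion anticipates that "a parsimonious set of injury-related and historical factors will predict opioid misuse".

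**The concern.** Survey fatigue explains why the ACE is not given at baseline. It does not explain why weeks 12 and 24 could not serve as a back-up. Among the instruments first given at week 4, the ACE is the only one that records fixed history. A missed week 4 craving or pain score cannot be reconstructed later, but a missed ACE could be supplied at any later contact.

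The outcome is scored at week 24, so a participant can miss week 4, return, have a known outcome and have no ACE score. The candidate rule then turns a small gap in data collection into an all-or-nothing result. If too many events lack the ACE, it leaves model building for everyone, including those who completed it. The plan would then lose a historical predictor for a reason unrelated to its predictive value. Because candidates are limited to baseline and week 4 variables, an ACE completed at week 12 or 24 would also have no clear status in the analysis.

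**Working it through.** **Inputs from the article (Aims 1 and 2: sample size calculations and analysis).** Analysable n = 221; incidence at least 8%; odds ratio 2.0 per SD; 80% power; 5% significance level; 25% drop-out; 295 recruited; candidate limit 5% of events.

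**Assumption not in the article.** m is the probability that an event case misses week 4 but still has a scored outcome, taken as independent between participants. The 25% drop-out figure is a different quantity and is not used for m.

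**Step 1: the plan's own figures.** The Hsieh formula for one continuous covariate, taken as two-sided, is n = (z_0.975 + z_0.80)² / [p(1 − p)(ln OR)²]. With p = 0.08 and OR = 2.0 it gives n = 221.96, or 222 rounded up, against 221 stated. Power at 221 is 79.8%. For recruitment, 221 / 0.75 = 294.7, or 295, as stated. The planning figures can therefore be used.

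**Step 2: events and the tolerance.** Expected events are 221 × 0.08 = 17.7, about 18, leaving 221 − 18 = 203 non-events. The limit is 0.05 × 17.68 = 0.88 event, which is less than one. One loss out of 18 is 1/18 = 5.6%, above 5%.

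**Step 3: chance that the ACE is excluded.** With 18 events and no loss tolerated, P = 1 − (1 − m)^18.

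| Assumed m | Expected event cases without ACE, 18m | P(at least one) | Non-events without ACE at the same rate, 203m |
|---|---|---|---|
| 3% | 0.5 | 42% | 6 |
| 5% | 0.9 | 60% | 10 |
| 10% | 1.8 | 85% | 20 |
| 15% | 2.7 | 95% | 30 |

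**Step 4: sensitivity to the number of events.** The article says at least 8%, so more events are possible. From 20 events one loss is tolerated (1/20 = 5.0%, not above the limit). The binomial chance of exceeding the limit is then:

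| Events (incidence in 221) | Losses tolerated | m = 5% | m = 10% | m = 15% |
|---|---|---|---|---|
| 22 (9.8%) | 1 | 30% | 66% | 86% |
| 35 (16%) | 1 | 53% | 88% | 98% |
| 44 (20%) | 2 | 38% | 83% | 97% |

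The exact one-case threshold belongs to the planned 8%. At m = 10% or more, exclusion remains more likely than not in every row. At m = 5% it is less certain.

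**The case against.** The strongest objection is that this rests on silence. Table 1 is a schedule and does not say what staff do with a form left undone. The article gives no visit windows or late-completion rules for any instrument, and a journal article commonly leaves these to the full protocol. That stands against one tempting inference, that a participant who misses week 4 loses the ACE permanently: late completion is neither provided for nor forbidden. It does not dispose of the point. Text and table both fix a single collection time, and the candidate rule as written recognises only baseline or week 4 variables.

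Other objections stand in part:

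- Mail or telephone completion at week 4 lowers the risk, and every miss rate used here is assumed.
- The sensitivity comes from applying a 5% rule to about 18 events, and one missing event would exclude any candidate. That is true, but for this fixed-history item the loss can be repaired afterwards.
- A reader might infer that the ACE is a main historical factor in the plan. The Discussion does not name it and the article does not rank it.
- A reader might also infer that catch-up would recover everyone with an outcome. That assumes full completion. It also assumes that the outcome is always established at week 24, whereas other sentences describe development during or within the 24 weeks.
- The article offers no evidence that missing week 4 is related to early opioid problems.

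**Conclusion.** The point holds as a small, avoidable weakness in data collection. It is not a contradiction or a wrong figure, since text and table agree. With about 18 expected events, one event case without an ACE excludes it from model building. The chance of that is about 42% to 95% for assumed, independent miss rates of 3% to 15%. These probabilities illustrate the rule and do not forecast what will happen. They apply where no late ACE is collected or admitted, and they matter only if the ACE would otherwise have passed the univariate screen.

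**What to change.** - **Table 1 and Independent variables:** give the ACE at week 4 and, if it was not obtained, at the next contact, preferably week 12 by mail or telephone and otherwise week 24.
- **Aims 1 and 2: analysis:** add one sentence that the ACE is treated as a baseline historical candidate whenever it was completed.
- **Safeguard:** flag late answers and repeat the analysis without them, because a few may be given after misuse has begun or, at week 24, alongside the outcome measures.

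The cost is a table footnote, one sentence, and a 10-item form carried forward for those who missed week 4. The benefit is limited to the ACE. A participant's other missed week 4 measures stay missing, so that person would still drop out of any complete-case model that includes them.
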